### Sample size

The sample size for the study has been calculated based on the pain domain of the FHSQ as the primary outcome measure [66]. Using a minimal important difference of 12.5 and a standard deviation of 23 obtained from a previous study [68], and assuming a 10% drop-out rate, the required sample size is 60 per group (power = 80%). We believe that the 10% drop-out rate is reasonable, as our recent randomized controlled trial of a multifaceted podiatry intervention to prevent falls in older people had a drop-out rate of less than 5% over a much longer period of follow-up (12 months) [71]. The extra precision provided by covariate analysis was conservatively ignored when performing this calculation.

### Evaluation of adherence

Adherence to the intervention will be documented at 4, 8, 12 and 16 weeks by asking participants on how many days (and for how many hours) they have worn their footwear, on average, in the past month.

### Complications and adverse events

Complications and adverse events associated with the intervention are unlikely. However, the questionnaires at the 4, 8, 12 and 16 week follow-ups will provide participants with an opportunity to report any difficulties they have with the footwear, and all adverse events will be reported in the final manuscript.

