**Methods:**

One hundred and twenty DVA clients with disabling foot pain residing in Melbourne, Australia, who are not eligible for medical grade footwear will be recruited from the DVA database, and will be randomly allocated to an intervention group or a ‘usual care’ control group. The intervention group will continue to receive their usual DVA-subsidized podiatry care in addition to being provided with low-cost, supportive footwear ([name]®, Vasyli Medical, Labrador, Queensland, Australia). The control group will also continue to receive DVA-subsidized podiatry care, but will not be provided with the footwear until the completion of the study. The primary outcome measure will be pain subscale on the Foot Health Status Questionnaire (FHSQ), measured at baseline and 4, 8, 12 and 16 weeks. Secondary outcome measures measured at baseline and 16 weeks will include the function subscale of the FHSQ, the Manchester Foot Pain and Disability Index, the number of DVA podiatry treatments required during the study period, general health-related quality of life (using the Short Form 12® Version 2.0), the number of falls experienced during the follow-up period, the Timed Up and Go test, the presence of hyperkeratotic lesions (corns and calluses), the number of participants using co-interventions to relieve foot pain, and participants’ perception of overall treatment effect. Data will be analyzed using the intention-to-treat principle.

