### Control group

The control group will continue to receive regular podiatry treatment as clinically required. This will typically include toenail maintenance and scalpel debridement of hyperkeratotic lesions (corns and calluses). Upon completion of the trial, they will be provided with the same footwear used in the intervention group.

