### Secondary outcome measures

Secondary outcome measures will be documented at baseline and 16 weeks and will include:

(i) the function domain of the FHSQ [3];

(ii) the functional limitation, pain intensity and concern about appearance subscales of the MFPDI [49];

(iii) the number of DVA podiatry treatments required during the study period;

(iv) general health-related quality of life, assessed with the Short Form 12® Version 2.0 [69];

(v) the number of falls experienced during the follow-up period;

(vi) functional mobility, using the Timed Up and Go test [70];

(vii) presence of hyperkeratotic lesions (corns and calluses);

(viii) number of participants using co-interventions to relieve foot pain (such as oral non-steroidal antiinflammatory medications, topical medications and visits to other health-care practitioners), documented using a diary at 4, 8, 12 and 16 weeks, and;

(ix) participants’ perception of overall treatment effect at week 16, assessed with the question ‘Overall, how has your foot pain changed since the start of the study?’ with a five-point Likert scale response (‘marked worsening’, ‘moderate worsening’, ‘same’, ‘moderate improvement’, or ‘marked improvement’). For the purpose of analysis, this scale will then be dichotomized, where ‘success’ is defined as marked or moderate improvement on this scale.

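### The only adverse-event prompt described concerns the study footwear, so events outside the listed outcomes have no stated collection route in controls

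*Protocol article*

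**What the plan says.** The section Complications and adverse events opens with the expectation that "Complications and adverse events associated with the intervention are unlikely". It then names one means of collection: the four follow-up questionnaires "will provide participants with an opportunity to report any difficulties they have with the footwear, and all adverse events will be reported".

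The Abstract says that the control group "will not be provided with the footwear until the completion of the study", and the Control group section agrees: "Upon completion of the trial, they will be provided with the same footwear used in the intervention group".

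Secondary outcome measures lists several items that bear on harm and limits none of them to one arm. They include "the number of falls experienced during the follow-up period", the presence of corns and calluses, co-intervention use "documented using a diary at 4, 8, 12 and 16 weeks", and a week 16 question, "Overall, how has your foot pain changed since the start of the study", whose answers include moderate and marked worsening. Primary outcome measure adds FHSQ pain at baseline and all four follow-up times. Statistical analysis provides chi-square or Fisher's exact tests and relative risks for nominal data.

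**The concern.** The section promises complete reporting of adverse events, but the prompt attached to that promise is about the study shoes. A control who develops a blister or a break in the skin has no study footwear to have difficulty with, and the article describes no other question that would bring the event to light. An intervention participant with the same event is invited to mention it.

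Attribution needs a comparator here. Participants are 65 or older with persistent, disabling foot pain, and both arms typically receive nail care and scalpel debridement, so some background foot and skin events are plausible whatever shoes are worn. Participants and investigators are also unblinded, and a prompt tied to the shoes adds to the existing risk of differential reporting. According to Trial status, the results will inform footwear provision in a departmental program. That decision would be better served by a harms statement that can separate the shoes from background.

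**Working it through.** The plan gives no adverse-event figure to reproduce, so the main check sets collection routes against events.

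**Step 1. Stated route in controls, by type of event**

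| Event | Stated route in controls | Section |
|---|---|---|
| Falls | Yes, count over follow-up | Secondary outcome measures (v) |
| Corns and calluses | Yes, baseline and 16 weeks | Secondary outcome measures (vii) |
| Worse foot pain | Yes, FHSQ pain, MFPDI pain intensity, global change | Primary outcome measure; Secondary outcome measures (ii), (ix) |
| Other treatment sought for foot pain | Yes, diary | Secondary outcome measures (viii) |
| Blister, skin break, ulcer | None stated | – |
| New pain outside the foot | None stated | – |

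Podiatry visit counts and the SF-12 may move with an event in the last two rows, but they do not record it. Corn and callus presence at 16 weeks would miss a blister or skin break that had healed.

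**Step 2. Group size**

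Inputs from Sample size: difference 12.5, SD 23, power 80%, drop-out 10%. Alpha is 0.05 from Statistical analysis, taken as two-sided.

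- n = 2 × (1.96 + 0.8416)² × 23² / 12.5² = 2 × 7.849 × 3.3856 = 53.1, rounded up to 54 per group.
- 54 / 0.90 = 60 per group, which agrees with the plan.

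**Step 3. Scale of what could go unrecorded**

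The documents give no rate. Assume that 5% to 20% of participants have an event of the last two types in 16 weeks, irrespective of footwear.

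- 60 × 0.05 = 3 controls; 60 × 0.20 = 12 controls.

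This is the number of controls with an event that the plan gives no stated way to record. It is not a forecast of the difference between arms.

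**Step 4. What each form of collection can support**

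- Footwear arm alone, no events seen: the exact one-sided 95% upper bound on the rate is 1 − 0.05^(1/60) = 4.9%, or 1 − 0.05^(1/54) = 5.4% with 54 followed up. This says nothing about background.
- Same question in both arms, 60 per group: power = Φ{[|p₁ − p₀| − 1.96 × √(2p̄(1 − p̄)/60)] / √[p₀(1 − p₀)/60 + p₁(1 − p₁)/60]}, where p̄ is the mean of p₀ and p₁.
 - Assumed 5% against 10%: (0.05 − 0.0943) / 0.0479 = −0.92, power about 18%.
 - Assumed 5% against 20%: (0.15 − 0.1183) / 0.0588 = 0.54, power about 70%.

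Symmetric collection makes a comparison unbiased by the prompt. It does not make it precise for uncommon events.

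**The case against.** Four arguments weigh against the point.

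- **Much relevant harm is already collected in both arms.** This stands. A reader might infer that harms are recorded in one arm only and cannot be compared at all. The outcomes in the first four rows of the table contradict that, and Statistical analysis supplies tests. The point is confined to what lies outside those outcomes.
- **The questionnaires are not shown, and a condensed article may omit form content.** This stands in part. The forms may contain a general adverse-event item, and the article does not call the footwear prompt the sole one. But the article does not merely leave the method out: it describes a method and ties it to the shoes. If a neutral item exists, one sentence settles the matter.
- **The section concerns events associated with the intervention, and shoe complaints can arise only in people wearing the shoes.** It is legitimate to describe those complaints in one arm. On this reading the reporting promise covers only such events. Even so, judging whether an event is associated with the shoes needs the background rate, which a footwear prompt cannot supply.
- **A footwear prompt need not capture unrelated events in the intervention arm either.** This stands. It would be tempting to predict 3 to 12 events in the intervention arm against none in controls. That requires full capture in one arm and zero in the other, which the documents do not support, and nothing says that background events will be charged to the shoes.

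**Conclusion.** The point holds in a limited form. As written, the plan asks about adverse events through a prompt that applies to one arm only. Events outside the planned outcomes therefore have no stated collection route in controls, a comparison of them would not be interpretable, and the reporting promise is not supported for that arm.

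The size cannot be derived from the documents. Under the assumed 5% to 20% rate, 3 to 12 of 60 controls would be affected; a lower rate gives fewer. The conclusion rests on the article describing the follow-up questionnaires accurately.

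A reader might also infer that repairing this would let the trial demonstrate safety. It would not: the stated aim is effectiveness, and 60 per group gives about 18% power for 5% against 10%. The primary analysis and sample size are untouched. This is a worthwhile repair to harms ascertainment, not a threat to the main result.

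**What to change.** At 4, 8, 12 and 16 weeks, ask both arms the same neutral adverse-event question or a short checklist that covers at least blisters, skin breaks or ulcers, and new pain outside the foot. Report participants with at least one event by arm, using the chi-square or Fisher's exact test and relative risk already specified. Keep difficulties with the footwear as a separate item, described in the intervention arm only. If the current forms already contain a neutral item for both arms, say so in Complications and adverse events; no other change is then needed.

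Trial status reports that recruitment began in October 2012, so a change reaches only the remaining contacts. The final report should state that any earlier collection was asymmetric and from when both arms were asked alike.

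The cost is a few tick-boxes at contacts already scheduled and more background events to report. Low precision for uncommon events will remain.

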### Statistical analysis

Statistical analysis will be undertaken using SPSS version 20.0 (IBM Corp, NY, USA). All analyses will be conducted on an intention-to-treat principle using all randomized participants. Multiple imputation will be used to replace any missing data using five iterations, with age, baseline scores, and group allocation as predictors [72]. Demographic characteristics and baseline data will be summarized by descriptive statistics. Continuous data will be explored for normality using standard tests to satisfy the assumptions of parametric statistics. If data are found to be not normally distributed, transformation will be attempted using conventional techniques [73]. However, if data are still not normally distributed after transformation, non-parametric statistical tests will be used. Continuously-scored primary and secondary outcome measures with a normal distribution will be compared between groups using a linear regression technique with baseline scores, adjusted for by the analysis of covariance model [74,75]. Nominal and ordinal scaled data will be compared using chi-square analyses (or Fisher's exact test where appropriate) and Mann–Whitney *U*-tests, respectively. Effect sizes will be determined using Cohen’s *d*[76] for continuous data and relative risks for nominal data. Statistical significance for hypothesis tests will be set at the conventional level of α = 0.05.

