### Primary outcome measure

The primary outcome measure will be the pain domain of the Foot Health Status Questionnaire (FHSQ). The FHSQ consists of 13 questions reflecting four foot health-related domains: foot pain, foot function, footwear, and general foot health [66]. The FHSQ pain domain comprises four questions, with higher scores representing better foot health (that is, 100 = best foot health and 0 = worst foot health). The FHSQ pain domain demonstrates a high degree of content, criterion, and construct validity (Cronbach α = 0.88), high retest reliability (intraclass correlation coefficient = 0.86) and has been used as an outcome measure in clinical trials for a range of foot disorders [67]. Previous research indicates that the minimal important difference for this measure is 12.5 points [68]. The FHSQ pain domain will be measured at baseline and at 4, 8, 12 and 16 weeks, with the primary endpoint being the 16 week score.

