## Discussion

Footwear plays an important role in the maintenance of foot health and mobility in older people, and it has long been recognized that suboptimal footwear can be detrimental [77,78]. The provision of appropriate footwear, therefore, has considerable potential to reduce pain and improve health-related quality of life in this age-group. Although several studies have been undertaken to assess the effectiveness of footwear interventions in reducing foot pain in people with rheumatoid arthritis and other degenerative foot disorders [79-81], none have focused on the general veteran community. The study outlined in this protocol is, therefore, novel in that it targets a specific group of veterans (those ineligible for medical grade footwear) and uses generic, off-the-shelf footwear as the intervention.

Participants will be followed up at four-weekly intervals up to 16 weeks. This is longer than previous footwear intervention studies, which have employed 8 week [79] or 12 week [80,81] follow-up periods. We are, therefore, confident that the duration of the study is sufficient to detect differences between the groups, if they exist. Furthermore, previous footwear studies have been limited to single baseline and follow-up assessments [79-81], whereas our study will incorporate five repeated measurements for the primary outcome measure (baseline, 4 weeks, 8 weeks, 12 weeks and 16 weeks). This will provide additional insight into the trajectory of any improvements in participants’ foot pain. However, to address the issue of multiple testing of serial measurements [82,83], we have pre-specified 16 weeks as the primary end-point, and no statistical comparisons of the 4, 8 and 12 week scores will be undertaken.

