There are three key limitations of the study design that warrant careful consideration. Firstly, due to the nature of the intervention, it will not be possible to blind participants to their group allocation, nor will it be possible to blind the investigators providing the intervention. Secondly, because the ‘usual care’ control group will receive no additional treatment until the completion of the study, there is a risk of what is often referred to as ‘resentful demoralization’. That is, participants allocated to the control group may be resentful of not receiving the intervention, which may affect their adherence to the tasks required of them in the study and systematically influence their responses to the outcome measure questionnaires [86]. While this cannot be completely avoided, it may be offset to some extent by the fact that the control group participants will receive the intervention footwear at the completion of the trial, free of charge - footwear that they would not otherwise be eligible for under the DVA program. One suggested approach to address this issue is to document participant group allocation preference as a prognostic variable and consider this in the statistical analysis [87]. However, this would not be appropriate in our study, as it is unlikely that any participants would prefer to wait 16 weeks for their footwear rather than receiving it at the commencement of the study. Finally, this trial has been pragmatically designed to ensure that the findings can be easily translated into ‘real world’ situations, where off-the-shelf footwear is most often purchased without clinical assessment or diagnosis from foot health professionals. As such, we have not restricted the inclusion criteria in relation to the underlying *cause* of foot pain, so it is possible that our sample will include some participants with conditions that may not be amenable to treatment with footwear.

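### The imputation model omits the 4, 8 and 12 week pain scores, so the week-16 estimate can be biased if drop-out follows interim pain differently by arm

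*Protocol article*

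**What the plan says.** Statistical analysis (protocol article) promises an intention-to-treat analysis of everyone randomized, with ANCOVA on the baseline score for normally distributed continuous outcomes. On missing data it states: "Multiple imputation will be used to replace any missing data using five iterations, with age, baseline scores, and group allocation as predictors".

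Primary outcome measure sets the schedule: "The FHSQ pain domain will be measured at baseline and at 4, 8, 12 and 16 weeks". Week 16 is the primary endpoint.

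The Discussion explains that the earlier scores are there to show the trajectory and that, to avoid multiple testing, "no statistical comparisons of the 4, 8 and 12 week scores will be undertaken".

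Sample size assumes 10% drop-out and cites a drop-out below 5% over 12 months in the team's earlier trial.

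The Discussion also says participants cannot be blinded. It names a risk of resentful demoralization in controls, "which may affect their adherence to the tasks required of them in the study and systematically influence their responses" to the questionnaires. It separately regards it as likely that some participants will be dissatisfied with the footwear, either when it is issued or later.

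**The concern.** The predictor list is stated and closed, and the term for baseline scores cannot be stretched to cover later visits. Someone who reports worse pain at week 12 and then leaves is imputed as if only age, baseline and arm were known. Repeated measurements of the primary outcome itself are set aside at the one point where they could inform a missing value.

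The missing-at-random assumption is therefore stronger than it needs to be. It treats drop-out as unrelated to follow-up pain once age, baseline and arm are known. In an open-label trial the article itself names influences particular to each arm: demoralization in controls and dissatisfaction with the shoes in the intervention group. At stake is the accuracy of the week-16 contrast, in a trial sized to detect 12.5 points with 80% power.

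**Working it through.** **1. The plan's own figure.** The Sample size section is based on "Using a minimal important difference of 12.5 and a standard deviation of 23 obtained from a previous study", with 80% power and 10% drop-out. Alpha is 0.05, taken as two-sided.

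n = 2 × (1.960 + 0.842)² × 23² / 12.5² = 2 × 7.849 × 529 / 156.25 = 53.1, so 54 per group. Then 54 / 0.90 = 60 per group. The stated figure is reproduced, and nothing below changes it.

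**2. Scale.** The standard error of the adjusted difference with 54 completers per group is 23 × √(1 − ρ²) × √(2/54), where ρ is the baseline to week-16 correlation. At ρ = 0.7 this is 3.16. A simulation with 60 per arm and multiple imputation gave about 3.2. At ρ = 0.5 it is 3.83. The article gives no ρ.

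**3. Why the stated model adds little.** Suppose only week 16 is missing. Fitted values from a regression on group and baseline lie exactly on the plane that the ANCOVA on group and baseline fits to the completers. Adding them leaves the group coefficient unchanged. Multiple imputation adds random noise around those values, and age contributes only what it predicts beyond baseline.

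**4. When bias arises.** Let p be an arm's drop-out proportion, and δ the average amount by which its imputed week-16 scores exceed what the drop-outs would have scored. Approximately,

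bias in (intervention − control) = p_I × δ_I − p_C × δ_C.

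Unequal p with δ = 0 gives zero. Equal p with equal δ also gives zero. Both ingredients are needed: δ different from zero, and p or δ differing by arm. For example, p_C = 0.15, δ_C = 15 points and δ_I = 0 give −0.15 × 15 = −2.25.

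**5. Size.** The true effect is 12.5 and the SD 23 (both from the article). The rest is assumed: the correlation pattern, and a log-odds of drop-out rising by 1.5 per SD of worse week-12 pain wherever dependence is stated. All drop-outs have weeks 4 to 12 observed. Figures are large-sample bias in points under the stated model, with age left out as uninformative.

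| Drop-out pattern | Exchangeable 0.5 | Exchangeable 0.7 | Baseline 0.5, follow-up 0.68–0.80 | Autoregressive 0.8 |
|---|---|---|---|---|
| 15% vs 5%, unrelated to pain | 0 | 0 | 0 | 0 |
| 10% vs 10%, same dependence in both arms | 0 | 0 | 0 | 0 |
| 15% vs 5%, same dependence in both arms | 0.6–0.7 | 0.6 | 1.4 | 1.4–1.5 |
| 10% vs 10%, dependence in one arm only | 0.7 | 0.6 | 1.5–1.6 | 1.7 |
| 15% pain-driven in one arm, 5% random in the other | 1.0 | 0.8–0.9 | 2.2–2.3 | 2.4 |

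The sign is negative when controls are the arm with more, or pain-driven, drop-out, and positive when it is the intervention arm.

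**6. Milder cases**, third correlation pattern:
- 5% in each arm, pain-driven in controls only: about −0.8.
- 7.5% control and 2.5% intervention, dependence in both: about −0.75.
- 15% and 5%, dependence in both at log-odds 0.7 per SD: about −0.8.
- Drop-out spread over the four intervals: −2.3 becomes −1.6, and −1.4 becomes −1.0.

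**7. With the interim scores added**, the large-sample bias was within 0.12 points of zero (simulation error) in every case driven by week-12 pain. With 60 per arm, nominal drop-out of 15% (intervention) and 5% (control), correlation 0.7 and dependence in both arms, the mean estimate was 13.07 under the stated model and 12.58 with the interim scores. The standard errors were 3.21 and 3.18.

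**The case against.** The strongest reply is that the consequence is conditional and may be small. A reader might infer that differential drop-out in itself biases the primary estimate. It does not: 15% against 5% unrelated to pain gives zero. Nor does the treatment contrast require drop-out to be unrelated to pain, because equal rates with equal dependence also give zero. The larger figures need a threefold difference in rates, dependence confined to one arm, and departures only after week 12. The article supports none of these in particular, and its cited experience of under 5% drop-out points to the low end. The direction is not fixed either. All of this stands, and it limits the point to a possible bias with a range that includes zero.

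A reader might also infer that the plan expects demoralized controls to leave. The Discussion speaks only of a risk that may affect task adherence and responses, and it offers free footwear at the end as a partial offset. Dissatisfaction with the shoes is a reason in the other arm. Where it arises at issue, there is no interim score to use and the remedy adds nothing.

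Two further complaints are not supported. No harm is shown from omitting sex from the imputation model. The reference to five iterations may simply mean five imputations in a condensed article. With about 10% missing information, five have relative efficiency 1/(1 + 0.1/5) = 98%. That interim scores are the best predictors of week 16 is plausible but undocumented.

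The reply does not justify leaving the scores out. The ban on comparing the interim scores between groups does not bar using them as predictors.

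**Conclusion.** The point holds in conditional form. The stated imputation model discards the interim pain scores and can bias the primary estimate if drop-out depends on interim pain and the rate or the dependence differs by arm.

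Under the assumed correlations and mechanisms, at 5% to 10% overall drop-out, the bias runs from 0 to about 2.3 points in either direction (2.4 under the autoregressive pattern). The upper end is 2.3/12.5 = 18% of the target difference. It is about 0.7 of a standard error of 3.2, or 0.6 of the 3.83 that goes with a baseline correlation of 0.5. Milder cases are mostly below 1.5 points. A contrived pattern, with dependence running in opposite directions in the two arms, reaches about 3.4, but nothing in the article suggests it.

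The case for change is a weaker assumption at no cost, not a gain in precision: the standard error moves by about 1% (3.21 to 3.18). That the primary estimate will be biased, or biased in a known direction, is not shown.

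**What to change.** In Statistical analysis, extend the predictors for the week-16 FHSQ pain score to age, group, the baseline score, and the FHSQ pain scores at 4, 8 and 12 weeks. Keep the ANCOVA on baseline as the primary analysis. Add a sentence saying that the interim scores enter only as imputation predictors and are not compared between groups, so that the Discussion's rule plainly still holds.

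The cost is one or two sentences of analysis wording. The data are already collected and 60 per group stands. The change does not help participants who leave before week 4, and it does not address drop-out that depends on pain not captured by the recorded scores.

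### If 'five iterations' means five imputed data sets, a primary p-value between about 0.02 and 0.08 depends noticeably on the random seed; raising the number to 50 or more is a minor, nearly free improvement

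*Protocol article*

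**What the plan says.** The Statistical analysis section analyses all randomized participants by intention to treat and handles missing values as follows: "Multiple imputation will be used to replace any missing data using five iterations", "with age, baseline scores, and group allocation as predictors". The week-16 FHSQ pain score is the primary endpoint (Primary outcome measure) and is compared by analysis of covariance on the baseline score. The decision threshold is explicit: "Statistical significance for hypothesis tests will be set at the conventional level of α = 0.05".

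The Sample size section sets the expected amount of missing data: "assuming a 10% drop-out rate, the required sample size is 60 per group". It defends the 10% by citing the team's earlier trial, which lost less than 5% over 12 months.

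The article gives no count of imputed data sets apart from the 'five iterations', and no seed.

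**The concern.** Multiple imputation fills the gaps with random draws, so the pooled estimate, standard error and p-value all carry simulation noise. That noise shrinks as the number of imputed data sets, m, grows. If m is 5, the same trial data can fall on either side of 0.05 depending on the seed.

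The Discussion takes care to protect a single primary test by ruling out comparisons at 4, 8 and 12 weeks. Under Trial status, the results are meant to inform the Department's footwear provision. It would be unfortunate if a borderline answer turned on a software setting that is cheap to change.

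The wording adds a second problem. 'Iterations' can mean imputed data sets or cycles of the imputation algorithm, and only the number of data sets governs this noise.

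**Working it through.** **Inputs from the protocol article.** Difference 12.5 and SD 23 ("Using a minimal important difference of 12.5 and a standard deviation of 23 obtained from a previous study"), 80% power, α = 0.05, 10% drop-out, 60 per group, five 'iterations', predictors age, baseline and group.

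**Assumptions not in the article.** m = 5; missing at random and equally in both arms; normal scores; age unrelated to outcome; baseline-to-week-16 correlation r of 0.3 to 0.5.

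**Step 1: reproduce the plan's own figure.** n = 2 × (1.96 + 0.842)² × 23² / 12.5² = 53.2, rounded up to 54 per arm. 54 / 0.90 = 60. The stated 60 per group is reproduced with a two-sided test. About 6 of 60 per arm are then expected to be missing.

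**Step 2: efficiency.** With a fraction of missing information (FMI) of about 0.10, relative efficiency is 1 / (1 + FMI/m) = 1 / (1 + 0.10/5) = 0.980. Little precision is lost.

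**Step 3: size of the seed noise, by formula.** The SD of the t statistic between seeds is about √(FMI/m).
- m = 5: √(0.10/5) = 0.141. A t of 1.98 ± 1.96 × 0.141 runs from 1.70 to 2.26, or p from 0.089 down to 0.024.
- m = 50: √(0.10/50) = 0.045, or p from 0.039 to 0.058.

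**Step 4: simulation.** 60 per arm, 6 missing per arm, imputation on age, baseline and group, ANCOVA, and Rubin's rules with small-sample degrees of freedom. Imputation was repeated under many seeds on the same data, with r = 0.5. The simulated FMI was about 0.11. For data whose p with very many imputations is about 0.05:

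| m | SD of t between seeds | 95% range of p over seeds |
|---|---|---|
| 5 | 0.17 | 0.025–0.109 |
| 10 | 0.11 | 0.031–0.084 |
| 20 | 0.08 | 0.036–0.073 |
| 50 | 0.05 | 0.040–0.063 |
| 100 | 0.04 | 0.043–0.059 |

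A separate simulation, anchored instead on a complete-case p of 0.05, gave 0.025–0.103 (r = 0.3) and 0.027–0.112 (r = 0.5) with m = 5. With m = 100 it gave 0.043–0.058 and 0.045–0.061.

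Other amounts of missing data, m = 5: at 5% missing the range is 0.032–0.082 (0.03–0.084 in the separate simulation); at 15% it is 0.021–0.133.

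**Step 5: where the verdict is at risk.** Share of seeds giving p < 0.05, by the p-value that very many imputations would give (10% missing):

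| p | m = 5 | m = 20 | m = 50 |
|---|---|---|---|
| 0.01 | 99.8% | 100% | 100% |
| 0.02 | 96.6% | 100% | 100% |
| 0.03 | 85.7% | 99.2% | 100% |
| 0.04 | 65.5% | 84.3% | 96.0% |
| 0.06 | 26.7% | 14.7% | 4.7% |
| 0.08 | 7.2% | 0.2% | 0.0% |
| 0.10 | 1.6% | 0.0% | 0.0% |

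**Step 6: how often it would matter in the planned trial.** True difference 12.5; two seeds applied to the same data.
- Residual SD kept at 23, 4,000 trials: the seeds disagree on p < 0.05 in 6.3% of trials with m = 5, 3.0% with m = 20 and 2.0% with m = 50. Power is 77.5%, 78.6% and 78.5%.
- The separate simulation, 1,500 trials: 4.1% with m = 5 and 1.6% with m = 50. At true differences of 7.5 and 10 it gave 6.9% and 7.1% with m = 5, and 1.7% and 2.5% with m = 50.

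The gap between 6.3% and 4.1% probably reflects the residual SD. Crediting the baseline correlation lowers it to 23 × √(1 − r²), which is 21.9 at r = 0.3 and 19.9 at r = 0.5, so fewer trials fall near the threshold.

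**The case against.** The strongest defence is that five imputations give a sound analysis. Rubin's rules build the finite number of imputations into the variance and the degrees of freedom, so the test remains valid. Efficiency is about 98% and the power cost about 1 point. A reader might infer that five is too few for 10% drop-out in general. The figures do not support that: it is few only for the stability of a p-value near 0.05. This part of the defence stands.

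Three further points also stand. The 0.025–0.11 range is the worst case, for a result exactly at the threshold. Seed dependence exists at any finite m, and even with 100 imputations the range still straddles 0.05. And five imputations do not stop an independent analyst from reproducing the result, as a reader might infer: any number is reproducible if the seed is kept, and a seed can properly be left to the analysis plan or program.

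The wording is also unsettled. If 'iterations' means algorithm cycles, the number of imputed data sets is simply not given in a condensed article. That would not be a finding, and the magnitudes above would not apply.

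The argument from the earlier trial's loss of under 5% helps less, because at 5% missing the range is still about 0.03 to 0.08. Nor does the defence give a reason to keep five when a larger number costs so little.

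**Conclusion.** This is a minor, nearly free improvement and not an error of validity. If five imputed data sets are meant, a primary p-value between about 0.02 and 0.08 depends noticeably on the seed. At the planned difference, moving to 50 imputations cuts two-seed disagreement by about 2.5 points (4.1% to 1.6%) or 4.3 points (6.3% to 2.0%), depending on the residual SD assumed. No bias, inflated type I error or effect on the sample size has been shown. The conclusion rests on the five-data-sets reading and on the assumptions listed in the working; the amount of missing data matters most to the width of the range.

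**What to change.** In the Statistical analysis section, replace the phrase about five iterations with wording such as: at least 50 imputed data sets (for example 50 to 100), pooled by Rubin's rules, with a pre-specified random seed. State the number of algorithm cycles separately if one is needed. The exact figure is a matter of preference; most of the gain is reached by 50.

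The cost is one line of text and some minutes of computing. Sample size, data collection and participants are unaffected. If algorithm cycles were meant all along, the same sentence resolves the ambiguity.
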